#### Lymphadenectomy

Lymph node dissection will be performed based on the *Dutch oncologic guidelines* and *Japanese gastric cancer treatment guidelines* (13-15). For D2 lymphadenectomy no pancreato-splenectomy is performed since this is associated with high post-operative morbidity and mortality (3). Furthermore, lymph node station 10 is not dissected during total gastrectomy since it is technically difficult and associated with poor prognosis when affected (3,13). Lymph node stations 1, 3, 4d, 4sb, 5-9, 11p and 12a are dissected during distal gastrectomy. Lymph node stations 1-3, 4d, 4sa, 4sb, 5-9, 11p, 11d and 12a are dissected

during total gastrectomy. All lymph node stations will be marked by the surgical team and presented to the pathologist for evaluation.

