## 3. STUDY DESIGN

### *Design*

The study design is a non-blinded multicenter prospectively randomized controlled trial. Analysis will take place on an intention-to-treat basis.

The participating patients are randomized for one of the 2 treatment arms. The experimental arm consists of the laparoscopic approach, whereas the control arm is the comparison to the conventional surgery, consisting of the open approach (figure 2).

[figure not shown]

**Figure 2: Treatment allocation. Based on tumor location patients will undergo either distal or total gastrectomy, according to the Dutch gastric cancer guidelines.**

*Duration*

The duration of the study will be 3 years of inclusion + 5 years follow-up.

*Setting*

This study takes place in a hospital setting. Recruitment of patients will occur at the outpatient clinic. Participating patients will receive either laparoscopic (experimental arm) or open (conventional surgery) gastrectomy at the surgical theater. Postoperative care takes place at the surgical ward of the participating hospitals.

*Quality of Life*

The regular postoperative care for patients that undergo a gastrectomy for gastric cancer consists of an annual outpatient visit for the follow-up period of 5 years. This visit is used to check for signs of recurrence of disease and metastases, as well as long term complications. In addition to this standard care quality of life questionnaires will be sent to the patients home address to check the long term effects of the surgical procedure.

*Cost-effectiveness*

To evaluate the cost-effectiveness of both study procedures, an important secondary study parameter, medical costs will be related to productivity and quality of life. All medical costs related to the study procedure will be collected up to five years after the operation. Quality of life will be measured as mentioned above. Furthermore, study participants will be asked to fill in the questionnaire SF-HLQ to measure the productivity after surgery (appendix 3). An expert from the UMC Utrecht Julius Center will do the final cost-effectiveness analysis.

*Blood samples*

Blood samples will be drawn at baseline, 6 hours postoperatively and on postoperative day 2. The aim is to monitor the CRP, leukocytes, haemoglobin and a panel of interleukines production to obtain an indication of the inflammatory response during the early postoperative course.

*Biobanking*

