### Total gastrectomy:

The patient is positioned in supine position under general anaesthesia. The conventional open total gastrectomy is performed by means of an upper midline laparotomy. In case of the laparoscopic procedure, 5 ports are used: a camera port (10mm), two working ports (5mm), an assisting port (5mm) and a port (12mm) for the liver retractor. Placement of all ports is done according to the surgeons preference. The minor and greater curvatures of the stomach are dissected. The left gastric artery and vein are transected at their origin. Next, the right gastroepiploic artery and the right gastric artery are transected at their origin. The postpyloric duodenum is cleaved by means of a linear endostapler. Subsequently, the distal esophagus is dissected from the left and right crus and mobilized. At the distal esophagus 2 support sutures are placed to pull the esophagus into the abdominal cavity, after which the distal oesophagus is cleaved. Frozen section histology of the tumor resection planes is performed to assess the radicality of the resection. Optional frozen section histology can be performed for detection of local tumor invasion and metastases. The greater omentum is resected for future side-studies. Subsequently, a transverse incision is performed to take out the stomach and greater omentum (figure 1, A). A hand-sewn jejunio-jejunostomy is created. Next, the actual esophagojejunostomy is performed. The formation of a jejunal pouch and the placement of a feeding jejunostomy should be performed according to the local hospital's policy.

[figure not shown]

**Figure 4: Maximally 5 trocar ports are used. Trocar positions: trocar 1 (5mm), 2 (5mm), and 4 (5mm) are used for instrumentation used during the LTG. The camera is inserted through trocar 3 (10mm), which is the location of the minilaparotomy (A) for the removal of the stomach as well. The liver retractor is inserted through trocar 5 (12mm).**

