### **6.1.2 Secondary study parameters/endpoints**

- Oncologic outcome:
  - Resection margins in millimeters
  - R0 resection (complete resection with no microscopic residual tumor)
  - Number of lymph nodes dissected
  - Number of tumor positive lymph nodes dissected
- Postoperative morbidity and mortality (19) (see appendix 1)
- Quality of Life: EQ-5D-5L, EORTC QLQ-30, EORTC QLQ-STO22 (see appendix 2)
- Cost-effectiveness: (see appendix 3)
  - SF-HLQ
  - Health care use
  - Costs of the procedure, hospital stay and re-interventions
  - Post-operative quality of life and productivity
- Readmission

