## **6.2 Randomisation, blinding and treatment allocation**

After completion of preoperative chemotherapy and signing informed consent at the outpatient clinic, participants will be randomized by means of an online random number generator, stratified by centre. Randomization will be performed by the coordinating investigator and directly provided to the participating centres. The data-analyst will be blinded for the procedure.

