## **7.5 Data Safety Monitoring Board (DSMB)**

The stop-criteria are:

- <70% complete resection without tumor residual in the proximal or distal surgical resection plane (R0) in one or both arms,
- >50% less than 10 lymph node harvested in one or both arms.

A data safety monitoring board will be assigned to evaluate the outcomes at 105 patients.

A DSMB is established to perform ongoing safety surveillance and to perform interim analyses on the safety data. This committee is an independent committee, which is composed of (names will be determined at a later stage).

None of the members have a conflict of interest with the sponsor of the study.

Criteria on which the DSMB may decide to terminate the trial prematurely:

- Clear evidence of benefit of laparoscopic gastrectomy
- Clear evidence of harm of laparoscopic gastrectomy
- External evidence, such as other trials or published data, not available during the start of this trial.

The advice(s) of the DSMB will only be sent to the sponsor of the study. Should the sponsor decide not to fully implement the advice of the DSMB, the sponsor will send the advice to the reviewing METC, including a note to substantiate why (part of) the advice of the DSMB will not be followed.

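### Pathologists who count nodes and read margins and R0 on the definitive specimen are not masked to the surgical approach, which leaves the oncologic secondary comparisons open to avoidable assessment bias

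*Protocol*

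**What the plan says.** Section 3 (Design) states: "The study design is a non-blinded multicenter prospectively randomized controlled trial". Section 6.2, the section on blinding, names one masked role: "The data-analyst will be blinded for the procedure". No outcome assessor is mentioned there.

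Section 5 (Lymphadenectomy) describes how nodes reach the laboratory: "All lymph node stations will be marked by the surgical team and presented to the pathologist for evaluation". The surgical team necessarily knows the approach. The protocol does not say that the pathologist is told it, and it gives no step that keeps it from the pathologist. At total gastrectomy there is also a reading during the operation: "Frozen section histology of the tumor resection planes is performed to assess the radicality of the resection".

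Section 6.1.2 lists four oncologic secondary endpoints, all of them pathology readings: "Resection margins in millimeters", R0 status, "Number of lymph nodes dissected", and the number of positive nodes. Sections 8.2 and 8.3 analyse binary variables by a chi-square test and non-Gaussian variables by Mann-Whitney, at P < 0.05.

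Section 7.5 uses two of these readings as stop criteria: R0 at the proximal or distal plane below 70%, and ">50% less than 10 lymph node harvested in one or both arms". Margin in millimetres is not among them.

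**The concern.** Masking the analyst protects the analysis but not the measurement, because the analyst measures nothing. The pathologist does measure. A node count reflects what the surgeon removed and also how many nodes were found in the specimen, so it depends partly on search effort. A pathologist who knows that a specimen comes from the newer technique might search harder, or less hard, than for an open specimen. Margin and R0 readings involve less discretion but are not free of it.

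At stake is the between-arm comparison of node count, margins and R0. The Summary says that there is no randomised trial in a Western population with locally advanced disease, so readers will use these comparisons to judge how laparoscopic resection performs oncologically. A reading bias could create a difference that is not there. It could also hide a real deficit.

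Hospital stay is hard to mask from the treating team. The definitive pathology report can largely be masked. Masking must be in place before the first specimen is read, so it belongs in the protocol rather than in a statistical analysis plan.

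**Working it through.** The protocol gives no figure on this point to reproduce. The calculations show how sensitive the comparisons would be if a reading bias existed. They do not estimate one.

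**Node count**

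Inputs:
- n = 105 per arm (section 4.4).
- Two-sided 5% level. Section 8.2 gives P < 0.05; two-sided is an assumption.
- Mann-Whitney test, treated as a z-test with efficiency 0.955 relative to the comparison of means (assumption).
- Node-count SD of 8, 10 or 12 (assumption; the protocol gives no SD). Table 1 gives medians and ranges only: 16 (3-33) open and 19 (2-53) laparoscopic.
- No true difference between arms; a reading bias of b nodes in one arm (assumption).

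Formula: δ = (b/SD) × √(105/2 × 0.955) = 7.081 × b/SD. The probability of a significant result is Φ(δ − 1.96) + Φ(−δ − 1.96).

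| SD | b = 1: δ | false significance | b = 2: δ | false significance |
|---|---|---|---|---|
| 8 | 0.885 | 14.3% | 1.770 | 42.5% |
| 10 | 0.708 | 10.9% | 1.416 | 29.4% |
| 12 | 0.590 | 9.1% | 1.180 | 21.9% |

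**R0**

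Inputs: a true R0 of 92% in both arms (the open-series figure in Table 1), 105 per arm, and a lower reading in one arm caused only by knowledge of the approach. Exact enumeration of the uncorrected chi-square test gives:

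| Reading shift | Chance of P < 0.05 |
|---|---|
| none | 5.2% |
| 2 points | 8.3% |
| 3 points | 11.8% |
| 5 points | 22.4% |

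**Stopping criteria**

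The DSMB looks at 105 patients, so about 52 or 53 per arm. Both rules are absolute thresholds within an arm. The probabilities are exact binomial tails for one arm.

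- R0 below 70% means at most 36 of 52, or at most 37 of 53. The probability is about 0.000002 if R0 is read at 92%, 0.003-0.004 at 85%, and 0.044-0.051 at 80%.
- More than half with fewer than 10 nodes means at least 27 patients. The probability is below 0.000001 if 20% of patients have fewer than 10 nodes, about 0.001 at 30%, and 0.054-0.070 at 40%.

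The Table 1 medians of 16 and 19 would still be 14 and 17 after a loss of 2 nodes, well above 10. Extra search in one arm would move that arm further from stopping.

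**The case against.** The strongest reply is that this rests on silence. The protocol openly declares the trial non-blinded, contradicts nothing here, and never says that the pathologist is told the approach. That is correct, and "may know" is the most that can be said. But section 6.2 does address blinding and leaves out the people who take the measurements.

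A second reply is that the calculation assumes its conclusion, since nothing in the documents supports a bias of 1 or 2 nodes, or its direction. This stands. The figures show sensitivity only. They also fall as the SD rises: a rough reading of the Table 1 ranges, assuming normality, suggests a pooled SD of about 10.4, which gives 10.5% and 27.5%.

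A third is that masking would be partial. Frozen sections may already have been read with the approach known, and the surgical team that dissects and marks the stations stays unmasked. This also stands, and it limits the gain to the definitive specimen.

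A reader might go further and infer that reading bias threatens the stopping decision, because R0 and node yield are also stop criteria. The documents do not support that. Margin in millimetres is not a stop criterion, and the two rules lie far from the protocol's own historical values. Nor does the protocol state a non-inferiority hypothesis or margin for oncologic outcome that a biased count would decide.

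**Conclusion.** The point holds as a modest, avoidable weakness in the secondary oncologic comparisons. Pathologists reading the definitive specimen may know the approach, and node count in particular can respond to how hard they look. If that led to a bias of 1 node, the false-significance rate would be about 9-14%; with 2 nodes, about 22-42%. Both ranges rest on an assumed SD of 8 to 12, no true difference between arms, and a bias whose existence, size and direction are unknown.

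The primary endpoint, postoperative hospital stay, does not depend on pathology. Reading bias would hardly ever trigger a stop: R0 as read would have to fall to about 80% in an arm before the chance of crossing the limit reached about 5%, against 92-93% in Table 1.

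**What to change.** In section 5, require that definitive pathology requests for trial patients carry the study number, the resection type (distal or total) and the station labels, but not the surgical approach. In section 6.2, list the pathologist who reads the definitive specimen as masked to the allocated arm. Leave intraoperative frozen sections and station marking by the surgical team as they are, and say that these are not masked.

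The cost is a trial pathology request form. No extra reader or procedure is needed, and sample size, power and significance level do not change. That this is cheap is a judgement, since the protocol does not describe the centres' pathology workflow. Masking will sometimes fail, for example when the approach becomes known through routine contact with the surgical team.

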#### Diagnostics:

- Gastroesophagoscopy and biopsy for histopathologic analysis (PA).
- Endoscopic ultrasonography.
- CT-abdomen.
- CT-thorax.

#### Preoperative policy

- Preoperative nutrition will be given to patients with >10% weight loss the last 6 months or a BMI <18kg/cm^2, according to the 2009 European Society of Clinical Nutrition and Metabolism (ESPEN) guidelines (16) .

#### Postoperative policy

To ensure fast recovery, the ERAS protocol is followed. A consensus meeting between the participating centers is organized to discuss the pre- and postoperative protocol (17).

- Epidural analgesia will be given following open gastrectomy only. Other analgesia can be given without limitations to reach adequate pain control.
- Urinary catheterization can be done when indicated.
- Enteral feeding via a jejunostomy catheter can be given to patients who underwent total gastrectomy, according to the local hospital's policy. No jejunostomy catheter will be placed following distal gastrectomy.
- At postoperative day 1, patients will be encouraged to start liquid oral feeding.
- Mobilization under supervision of a physiotherapist starts as soon the patient is stable.
- Nasojejunal tubes for decompression will not be used (17).

However, the treating physician may implement a deviation from the protocol to avoid causing any harm or if there is a safety hazard to trial subjects without prior approval from the ethics committee.

## **6. METHODS**

### **6.1 Study parameters/endpoints**

#### **6.1.1 Main study parameter/endpoint**

- Postoperative hospital stay (days)

The following criteria have to be met:

- Adequate pain control with oral pain medication

- Started with mobilisation
- Adequate intake according to nutritional demand and being independent of supplementary intravenous fluids

### **6.1.2 Secondary study parameters/endpoints**

- Oncologic outcome:
  - Resection margins in millimeters
  - R0 resection (complete resection with no microscopic residual tumor)
  - Number of lymph nodes dissected
  - Number of tumor positive lymph nodes dissected
- Postoperative morbidity and mortality (19) (see appendix 1)
- Quality of Life: EQ-5D-5L, EORTC QLQ-30, EORTC QLQ-STO22 (see appendix 2)
- Cost-effectiveness: (see appendix 3)
  - SF-HLQ
  - Health care use
  - Costs of the procedure, hospital stay and re-interventions
  - Post-operative quality of life and productivity
- Readmission

### **6.1.3 Other study parameters**

Baseline characteristics:

- Gender
- Age
- ASA-classification
- Body Mass Index
- Comorbidities
- Sarcopenia (see appendix 8)
- Intoxications
- Perioperative chemotherapy

Postoperative outcomes:

- Operation characteristics:
  - Duration of surgery
  - Blood loss during operation
  - Conversion to alternative surgical procedure

- Postoperative course:
  - Duration of Intensive Care stay
  - Duration of Medium Care stay
  - Mechanical ventilation
  - Vital signs (heart rate, blood pressure, temperature)
- Overall survival
- Disease free survival (absence of local or distant recurrence)
- Patients experience:
  - Pain: VAS-score (see appendix 4)
  - Time to return to daily activity (days)
  - Time to return to normal nutritional regime (days)
- Weight at day 5 after surgery or at discharge in case of discharge before day 5.
- Ergonomics surgeon: SMEQ questionnaire (see appendix 5)
- Learning curves of participating centers

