### 4.4 Sample size calculation

The primary outcome parameter is postoperative hospital stay. A recent meta-analysis has shown that laparoscopic procedure shortens the median hospital stay with 4 days (12).

Hospital stay after laparoscopic gastrectomy: 14 days

Hospital stay after open gastrectomy: 18 days

Significance level ( $\alpha$ ) = 0.05

Power ( $1-\beta$ ) = 0.80

Sample size:

Total number of 210 participants:

- Laparoscopic gastrectomy (experimental arm) = 105
- Open gastrectomy (conventional surgery) = 105

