### 8.3 Other study parameters

Binary variables will be displayed in cross-tabulations. The Person  $\chi^2$  will be used for analysis between groups.

Variables with a non-Gaussian distribution and will be analysed by means of a Mann-Whitney-U test in univariate analysis.

Statistical significance is defined as  $P < 0.05$ .

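### Postoperative weight is listed as absolute weight with only unadjusted tests, so its comparison is unbiased but needlessly imprecise; the pre-operative weight should be used

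*Protocol*

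**What the plan says.** Protocol section 6.1.3 (Other study parameters) includes among the postoperative outcomes "Weight at day 5 after surgery or at discharge in case of discharge before day 5". The line names no change, percentage loss or reference weight. The baseline part of the same section lists "Body Mass Index", which cannot be obtained without a weight, but it gives no date for that weight and does not connect it to the postoperative one.

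Section 8.3 covers the analysis of these parameters. It gives a chi-square test for binary variables and, for the rest, "Variables with a non-Gaussian distribution and will be analysed by means of a Mann-Whitney-U test in univariate analysis", with significance at P < 0.05. It mentions no baseline adjustment and names no test for a continuous variable that is taken as Gaussian.

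According to section 6.2, "participants will be randomized by means of an online random number generator, stratified by centre"; body size is not a stratification factor. Section 4.4 sizes the trial at 105 per arm for hospital stay alone. No SD, expected difference or power is given for weight.

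**The concern.** Adults differ in weight by far more than any one of them is likely to gain or lose in five days. A comparison of absolute weights carries all of that between-patient spread as noise, whereas the effect of interest is plausibly one or two kilograms. The pre-operative weight explains most of the spread, and the baseline BMI implies that it is measured.

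If the outcome is analysed as listed, a null result would say almost nothing about a difference of 1 to 2 kg. Within one arm, a day-5 weight with no reference says nothing about loss. The item stands in the same list as time to return to a normal nutritional regime, which suggests a nutritional purpose that the raw figure serves poorly.

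**Working it through.** **The plan's own figure.** There is none for weight. The 210 patients in section 4.4 relate to hospital stay (18 versus 14 days, 80% power), for which no SD is stated. That figure therefore cannot be reproduced and has no bearing here.

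**Inputs from the protocol.** n = 105 per arm (section 4.4); P < 0.05 (section 8.3), taken as two-sided because sidedness is not stated.

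**Assumed inputs, not in the protocol.** SD of body weight 12, 15 or 18 kg; between-arm difference 1 to 3 kg; correlation r between pre- and postoperative weight 0.95 to 0.98.

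**Step 1: raw weight.** SE = SD × √(2/105) = SD × 0.1380. Power = Φ(d/SE − 1.96) + Φ(−d/SE − 1.96). Difference detectable with 80% power = 2.8016 × SE.

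| SD (kg) | SE (kg) | Power, 1 kg | Power, 2 kg | Power, 3 kg | Detectable (kg) |
|---|---|---|---|---|---|
| 12 | 1.66 | 9.3% | 22.7% | 44.1% | 4.6 |
| 15 | 2.07 | 7.7% | 16.2% | 30.5% | 5.8 |
| 18 | 2.48 | 6.9% | 12.7% | 22.7% | 7.0 |

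The Mann-Whitney efficiency factor of 0.955 for normal data lowers these slightly (15.7% instead of 16.2% at SD 15 kg and 2 kg). To reach 80% power for 2 kg at SD 15 kg, raw weight would need 2 × 2.8016² × 15² / 2² ≈ 883 patients per arm.

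**Step 2: using the pre-operative weight.** SD of change = SD × √(2(1 − r)). Residual SD after baseline adjustment (ANCOVA) = SD × √(1 − r²). At SD 15 kg and r = 0.95 these are 15 × √0.10 = 4.74 and 15 × √0.0975 = 4.68 kg.

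| SD (kg) | r | SD of change (kg) | Power, 2 kg, change | Adjusted SD (kg) | Power, 2 kg, adjusted |
|---|---|---|---|---|---|
| 12 | 0.95 | 3.79 | 96.8% | 3.75 | 97.2% |
| 12 | 0.98 | 2.40 | >99.9% | 2.39 | >99.9% |
| 15 | 0.95 | 4.74 | 86.3% | 4.68 | 87.2% |
| 15 | 0.98 | 3.00 | 99.8% | 2.98 | 99.8% |
| 18 | 0.95 | 5.69 | 72.1% | 5.62 | 73.2% |
| 18 | 0.98 | 3.60 | 98.1% | 3.58 | 98.1% |

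At SD 15 kg the difference in change detectable with 80% power is 2.8016 × 4.74 × 0.1380 = 1.8 kg (r = 0.95) or 2.8016 × 3.00 × 0.1380 = 1.2 kg (r = 0.98).

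**Step 3: bias and error rate, with the test the protocol names.** Simulation of 4,000 trials per scenario, 105 per arm, baseline weight with mean 75 and SD 15 kg, mean loss 3 kg with SD 2.5 kg (all assumed):

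| True difference (kg) | Mean raw contrast (kg) | Mann-Whitney rejects, raw | Mann-Whitney rejects, change |
|---|---|---|---|
| 0 | −0.04 | 5.0% | 4.4% |
| 1 | 1.00 | 8% | 80% |
| 1.5 | 1.52 | 10% | 99% |
| 2 | 1.98 | 15% | 100% |

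The raw contrast is centred on the true difference and its type I error is 5%. Its standard error is about 2.1 kg, against 0.34 kg for change.

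**The case against.** The strongest objection is that section 6.1.3 is a shorthand list of what is recorded. Vital signs and pain scores are listed there without a summary measure either, and the weight line does not rule out an analysis of change. A statistical analysis plan, which is not at hand, could derive it. That is a fair reason to rate the point low. It does not remove it: the protocol writes an absolute weight and names only unadjusted tests, so an analyst who follows it as written would use the weak comparison.

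Three stronger readings are tempting and should not be adopted.

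- A reader might infer that the raw comparison measures how heavy the patients are and not the effect of the operation. Under randomisation the expected between-arm difference in day-5 weight equals the expected difference in weight change, and the simulation agrees. A chance imbalance in body size adds noise that the 5% level already allows for; it is not an added bias.
- A reader might infer that section 8.3 imposes an unadjusted Mann-Whitney test on weight. It does so only if weight counts as non-Gaussian, which the protocol does not say. If weight is taken as Gaussian, no test is named. In neither case is adjustment provided for.
- A reader might infer that the outcome has no useful power at all. Low power is shown only for differences of about 1 to 3 kg under assumed SDs. Differences of about 5 to 7 kg would still be detectable, and the protocol makes no power claim for weight that could be contradicted.

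It is also fair that a stored, dated pre-operative weight is inferred from the BMI and not stated.

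**Conclusion.** The point holds as a matter of precision in an exploratory outcome. As listed, the comparison is valid but has about 13% to 23% power for 2 kg, where the same patients could give 86% to over 99% at SD 15 kg. Over the whole assumed range of SD 12 to 18 kg and correlation 0.95 to 0.98, power with the baseline used is 72% to over 99%. The SD, the correlation and the 2 kg difference are all assumptions, but raw weight is far weaker in every combination tried.

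The primary outcome, the secondary outcomes, the stopping criteria and the sample size do not depend on this item. It is an optional improvement.

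**What to change.** In section 6.1.3, state that the pre-operative weight underlying the baseline BMI is recorded in kilograms with its date, and that it is the reference for the weight at day 5 or earlier discharge. In section 8.3 or the statistical analysis plan, state that postoperative weight is compared between arms adjusted for that reference weight (ANCOVA). Alternatively, state that change from it is compared, which can keep the Mann-Whitney test. The two options have nearly the same power, so either will do. Percentage change was not evaluated here, and there is no evident reason to prefer it.

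The cost is one line in each place and, if the weight is not already stored with the BMI, one dated field on the case report form. No extra patients or visits are needed.
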